## Abstract

**Background:**

Graft-versus-host disease (GvHD) remains a major complication and limitation to successful allogeneic hematopoietic stem cell transplantation. Treatment of GvHD is challenging due to its heterogeneous nature of presentation, with steroids remaining the established first-line treatment. Long-term doses of systemic corticosteroids have many well-known side-effects including muscle atrophy. Despite the fact that reports in non-cancer clinical populations treated with glucocorticoids demonstrated that resistance training can reverse atrophy and weakness, no RCT has evaluated the potential of resistance training on preventing the disease- and treatment-induced loss of skeletal muscle mass and function in GvHD patients yet. In this context, ensuring adequate nutrition is important as protein deprivation may accelerate the wasting process. As GvHD patients are commonly found to be malnourished, nutritional medical care should be considered when investigating the effect of exercise in GvHD patients. Therefore, the aim of the present “Impact of Resistance Exercise and Nutritional Endorsement on physical performance in patients with GvHD” – Study (IRENE-G) is to evaluate the effects of resistance exercise in combination with nutritional endorsement on physical, nutritional and patient-reported outcomes in GvHD patients.

**Methods:**

IRENE-G is a 24-week prospective interventional RCT. One hundred twelve participants will be randomly allocated (1:1) to one of two arms: resistance exercise and nutritional optimization (experimental) vs. nutritional optimization only (control). Participants in the experimental group will engage in a supervised, progressive moderate-to-high intensity resistance training that is consistent with exercise guidelines for cancer patients, while additionally receiving nutritional support/therapy. Subjects of the control group solely receive nutritional support/therapy based on individual needs. Participants will be assessed at baseline, at 8, 16, 24 weeks for physical performance and various physiological, nutritional and patient-reported outcomes. Follow-up will be 6 months after intervention completion.

**Discussion:**

To our knowledge, this will be the first RCT to assess and compare the effects of a resistance intervention supplemented by nutritional support/therapy against nutritional support only on various health-related outcomes in GvHD patients. The study will contribute to our understanding of the value of exercise and nutritional endorsement in counteracting the negative consequences of GvHD and its treatment.

**Trial registration:**

ClinicalTrials.gov: NCT05111834. Registered 8 November 2021 – Retrospectively registered.

## Background

### Allogeneic hematopoietic stem cell transplantation and Graft-versus-host disease

Allogeneic hematopoietic stem cell transplantation (allo HSCT) is a potentially curative treatment modality for various malignant and non-malignant diseases [1]. In 2019, almost 20,000 allo HSCT were performed in Europe [2]. A major barrier for successful allo HSCT represents the Graft-versus-host disease (GvHD), as it remains the main cause for transplant-related morbidity and mortality [3–10]. The incidence of GvHD ranges widely, depending on various patient- and transplant-related variables. Roughly, 30–50% of patients develop an acute form of GvHD [3, 11–13]. The aggregated cumulative incidence for the chronic form of GvHD is estimated to be 30–50% [14, 15]. Risk factors for both forms of GvHD include degree of human leukocyte antigen mismatch, older donor age and donor-recipient gender mismatch [16]. A GvHD may appear in many different ways and can manifest in multiple organs e.g. lung, liver, skin and gastrointestinal tract. Consequently, patients suffer from organ-specific symptoms such as diarrhea, nausea, vomiting, exanthema, shortness of breath. The clinical manifestation has implication for patients’ physical function, limiting a patient’s ability to carry out activities of daily living and subsequently reduces the quality of life [6, 17–22].

Impairments in the physical domain is a result of both the disease itself and its treatments. Currently, the first-line therapy for both acute and chronic GvHD consists of glucocorticoids alone or in combination with calcineurin inhibitors, with solely 40–50% of patients responding adequately [23, 24]. Unfortunately, usage of glucocorticoids is associated with a variety of side-effects, especially at higher doses and with longer duration of therapy, such as osteoporosis, osteonecrosis, diabetes and myopathy with weakness primarily found in the proximal lower muscles, with particularly the pelvic girdle muscles being involved [23, 25, 26].

In view of the poor treatment respond and the toxic effects of the GvHD therapy, new supportive strategies that will help maintain or even improve patients’ quality of life are needed. Such supportive therapies should particularly target the physical domain, hence, reducing impacts on activities of daily living resulting in the preservation of public participation and autonomy.

### Physical function and exercise in the cancer/HSCT setting

There is strong scientific evidence that exercise can ameliorate the detrimental effects of cancer and its treatment. These beneficial effects include increases in physical fitness (i.e. aerobic capacity and muscle strength) and quality of life, improvements/prevention of lymphedema symptoms, reductions in fatigue, anxiety and depressive symptoms [27]. Furthermore, a growing body of evidence suggests positive effects of exercise on cancer-specific as well as all-cause mortality [28]. Hence, experts recommend cancer patients to participate in moderate-intensity aerobic training for a minimum of 30 min on 3 days per week and additional resistance training for at least two times per week [27]. Benefits of exercise can also be observed in the HSCT setting. A 2021 systematic review [29] yielded that exercise interventions may be beneficial on physical functioning and quality of life in patients undergoing HSCT. The findings of the positive effects of exercise on HSCT patients are supported by another review which found beneficial effects for muscle strength and physical fitness [30]. Specifically in patients receiving an allo HSCT, randomized controlled studies [31–35] showed that exercise is capable of counteracting the negative consequences of cancer and its treatment and may improve survival [36]. Despite such benefits, however, to date there is no scientific evidence of the effects of a structural exercise intervention in a subgroup of GvHD patients, specifically not among patients treated with high-dose steroids. Pre-clinical findings in a chronic GvHD murine model under standard immunosuppressive therapy suggest beneficial effects of exercise on survival, clinical course of GvHD and on physical capacity in the exercising mice group compared to control animals. Moreover, the exercising mice showed lower TNF-α and IL-4 levels after 12 weeks post transplant, reflecting a weaker inflammatory state [37]. These findings give first insight on how exercise may affect the clinical and biological course of GvHD patients. Unfortunately, not only the GvHD per se deteriorates the patients’ health status but also the treatment with corticosteroids. A prospective study authored by Morishita et al. [38] showed that the cumulative corticosteroids dose is associated with weak handgrip and knee extension. This is in line with recent findings of a small single-arm cohort study by Ngo-Huang et al. [39], who investigated acute GvHD patients on high-dose steroids and their decline in objective functional tests. They found a significant association between cumulative corticosteroid dose and the following functional tests: 6 min walk test, hip flexors and knee flexors strength, manual muscle testing strength, 5 sit to stand test. In terms of the timing of the decline, weakness can be detected as early as day 14, suggesting that early supportive interventions are needed to mitigate these changes. Interestingly, Morishita et al. [38] found that physical therapy is positively associated with physical function, indicating that exercise may be capable of ameliorating the detrimental effects of GvHD and its treatment. Given the fact that exercise has shown promise in counteracting the negative consequences of allo HSCT and can be considered as safe and feasible [30], there is a strong rational that it might be capable of ameliorating the detrimental effects of a GvHD too.

### Nutritional interventions in the Cancer/HSCT Setting

In order to encounter the decrements in physical performance and further side-effects in GvHD patients, ensuring adequate nutrition is important as protein deprivation may accelerate the loss in skeletal muscle mass and function. The nutritional status of cancer patients can vary significantly throughout the cancer continuum, with malnutrition often occurring [40–42]. According to the European Society for Clinical Nutrition and Metabolism expert group, approximately 10–20% deaths of patients with cancer are attributed to malnutrition rather than to the disease itself [43]. Further, cancer- and treatment-related malnutrition has been shown to be associated with increased morbidity [44], altered quality of life, particularly in the physical functioning scale [45–48], psychosocial stress [49], increased hospital length of stay [41, 50, 51] and increased healthcare costs [51]. Hence, nutritional support is an important aspect of cancer care. Malnutrition often involves cachexia, a multifactorial syndrome which is characterized by loss of skeletal muscle mass with or without loss of fat mass that leads to progressive functional impairment [52]. This condition is often accompanied by anorexia, which is driven by disturbances of the central mechanisms controlling food intake, resulting in loss of body weight, alterations in body composition and decline in physical function [53]. Patients undergoing allo HSCT are at an increased risk for these conditions, due to the toxic effects of treatments and/or due to secondary complications such as infections or GvHD [53, 54]. Studies report that a considerable number of patients undergoing allo HSCT suffer from worsening in their nutritional status during hospitalization and after discharge [55, 56]. Particularly patients with GvHD are vulnerable to malnutrition, as symptoms related to the disease and its treatment are driving forces for this condition (e.g. nausea, vomiting, mucositis of the mucous membrane of the upper gastrointestinal tract) [55, 57]. A study authored by Bassim et al. [58] reported a prevalence of malnutrition among chronic GvHD patients of 29%, highlighting the need for nutritional support in this specific population. The authors also reported that malnourished chronic GvHD patients have poorer survival compared with those without malnutrition and that malnutrition is associated with gastrointestinal tract, lung and mouth manifestations and impaired functional status and quality of life [58]. An even higher incidence of malnutrition among GvHD patients has been found in a study by Jacobsohn et al. [59]. According to their analysis 43% of GvHD patients were considered as malnourished [59]. Despite the incidence and adverse effects of malnutrition, the condition is often overlooked. However, addressing malnutrition at an early stage is important to mitigate nutritional derangements as soon as possible and maintain skeletal muscle mass and physical performance.

Nutritional intervention approaches seem to be effective in counteracting malnutrition in cancer patients. A review by Lee et al. [60] found that nutritional counselling with or without oral nutrition supplements is associated with improvements in different aspects of nutritional status outcomes including weight gain and maintenance, BMI and patient-generated subjective global assessment score in cancer patients.

### Combined exercise and nutritional support

Given nutrition’s foundational importance for various health-outcomes and for physical aspects, it is likely that a combination of an exercise and nutritional intervention will be of greater benefit than one intervention in isolation. Previous reviews which investigated the effects of combined nutritional and exercise interventions in incurable and colorectal cancer patients found improvements in multiple domains, including physical endurance [61, 62], suggesting that a combined approach may also be effective in other cancer populations. Despite the promising results of a combined exercise and nutrition program, a recent review by Prins et al. [29] showed that, to date, there is no study using such an approach in the HSCT setting. The IRENE-G study (acronym for Impact of Resistance Exercise and Nutritional Endorsement on GvHD symptoms) addresses the research gap and aims to examine the effect of a progressive moderate-to-high intensity resistance exercise program (2x/week for a total duration of 24 weeks) in combination with nutritional optimization on physical performance in GvHD patients treated with high-dose steroid therapy. To the best of our knowledge, this is the first RCT that specifically focuses on GvHD patients. The results of the IRENE- G study will enhance our understanding of the effectiveness of exercise interventions in combination with structured nutritional therapy measures for acute and chronic GvHD.

## Methods/design

### Study design

The IRENE-G study is a 24-week prospective, randomized, controlled, intervention trial with a two-armed parallel design and 1:1 allocation ratio of GvHD patients treated with systemic steroids.

The study examines and compares the effects of a supervised resistance exercise intervention and a nutritional optimization program (experimental group) against a nutritional optimization program only (control group) on physical performance in GvHD patients treated with steroids. The investigators hypothesize that both groups will benefit with regard to physical performance after 24-weeks, however, the authors assume that the effect will be significantly greater in the experimental group compared to the control group. Moreover, the investigators hypothesize that the experimental group will have lower levels of fatigue, less perceived GvHD symptom burden, a higher perceived quality of life, better muscle strength values and a higher vastus lateralis muscle volume, a better nutritional status as well as a better submaximal endurance capacity compared to the control group.

The flow through the IRENE-G study is presented in Fig. 1. The research will be conducted at a single site (University Hospital Heidelberg, Germany). Upon written informed consent, eligible patients will be randomly assigned to the experimental or control group. Patients in the experimental group will take part in a 24-week supervised resistance exercise program and a nutritional optimization program. The moderate-to-high intensity resistance exercise sessions will be performed for a duration of 60 min two times a week. Patients in the control group receive nutritional optimization only. The interventions will start directly after the completion of the baseline measurements (t0). Further assessments will take place 8 weeks (t1), 16 weeks (t2), and 24 weeks (t3, primary endpoint assessment) after baseline assessment. A follow-up assessment (t4) is planned 48 weeks after baseline. All assessment points are embedded into medical care/ outpatient visits.

**Fig. 1 Fig1:**
[figure not shown]
Study flow

The study will be performed in accordance with the Declaration of Helsinki and has been approved by the Medical Ethic Committee of the University of Heidelberg (number S-433/2021). Any protocol amendment which may impact the study conduct (e.g. changes to outcomes or eligibility criteria) will be communicated to and needs approval of the ethic committee prior to implementation. The Study Protocol has undergone full external peer review by the funding body as part of the peer review process in the Funding Declaration. This study protocol is written in accordance with the SPIRIT guidelines. The study is registered at ClinicalTrials.gov (NCT05111834).

### Study outcomes

An overview of the outcome measures used in the IRENE-G study, including the time of data collection can be viewed in Table 1. The analysis metrics of interest are difference between the treatment arms throughout the study and change from baseline to t3.

**Table 1 Tab1:** Study outcomes, instruments and assessment points

Outcomes	Instrument	t0	t1	t2	t3	t4
*Primary endpoint*						
Physical performance	Short Physical Performance Battery	x	x	x	x	x
*Secondary endpoints*						
Muscle strength	Hand-grip test, Hand-held Dynamometer	x	x	x	x	x
Muscle volume	Ultrasound	x			x	x
Submaximal endurance capacity	6 minutes walk test	x	x	x	x	x
Nutritional status	NRS 2002, hand- grip test, serum albumin, total protein levels	x	x	x	x	x
Quality of life	EORTC QLQ-C30/ HDC-29	x	x	x	x	x
Fatigue	EORTC QLQ-FA 12	x	x	x	x	x
GvHD Symptom burden	Modified 7-day Lee cGvHD Symptom Scale	x	x	x	x	x
Performance status	Karnofsky Performance Scale	x	x	x	x	x
*Others*						
Socio-demographic factors	Sex, age, marital status, family and living situation, education, employment status and smoking behavior	x			x	x
Physical activity (history)	Physical activity pre-diagnosis and during the intervention	x	x	x	x	x
Amnestic variables, medical history	Date of diagnosis, subtype of disease, remission status, conditioning regime, history of therapy, date of allo HSCT transplantation, HLA compatibility and comorbidities will be recorded from medical records	x				
Anthropometric data	Weight, height	Weekly				
Concomitant medication	Medical log	At each medical outpatient visit				
GvHD course	Physician rating	At each medical outpatient visit				
Adverse events	Medical records, reports of the exercise therapists and/or patient	Surveillance throughout the study				
Adherence to the exercise intervention	Self-reported and objective measures (e.g. attendance, exercise log, target intensity) of the intervention arm only	Surveillance throughout the study				

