#### Nutritional status

Nutritional status will be screened and adopted regulatory and performed individualized with multiple tools. First, the Nutritional Risk Screening (NRS 2002), a validated screening tool for detecting malnutrition in hospitalized settings, is used [94]. NRS includes a pre-screening, containing four yes/no-questions about body mass index, weight loss, food intake and disease severity. By answering at least one question with yes, the main screening will be performed, specifying and ranking the questions from pre-screening and also considering patients age. A total score > 3 implements a risk for malnutrition and requires further nutritional adjustment. Scores < 3 require regular repetition.

Based on NRS an individual nutritional counselling according to nutritional guidelines of the German Society for Nutritional Medicine and the European Society for Clinical Nutrition and Metabolism is performed. Weekly counseling includes monitoring of relevant blood parameters (e.g. serum albumin and total protein) and ensuring the daily calorie (25-30 kcal/kg bodyweight/d) and protein needs (1.2–1.5 g protein/kg body weight/d) are fulfilled. Finally, hand grip strength (see section muscle strength), known as a marker of muscle function and good nutritional state is performed regularly [95, 96].

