### Nutritional intervention

The nutritional status of participants of the control and of the experimental group will be examined at t0 using the NRS 2002, measurements of the hand grip dynamometer and medical/laboratory data which were collected during the latest clinical practice (e.g. weight, blood parameters like total protein, albumin, c-reactive protein, electrolytes as sodium, potassium, magnesium, phosphate, kidney and liver values, glucose, triglyceride). Based on participants individual needs and/or changes in general condition/nutritional status, nutritional recommendations are given. If malnutrition or a risk for malnutrition is detected, first step will always be oral supplementation, e.g. with protein supplements or oral nutritional supplements. In severe cases a nutritional therapy with e.g. enteral or parental infusion therapy will be initiated. Study participants will be contacted weekly to adapt nutritional therapy.

Throughout the study, nutritional recommendations and therapy will be adapted based on the risk of malnutrition (NRS 2002 score ≥ 3, low hand grip strength (men < 30 kg; women < 20 kg) defined as at least two standard deviations below the mean of the norm value, low serum albumin (< 30 g/l) and total protein (< 60 g/l)).

The main nutritional intervention is based on the scheme by Virizuela et al. [102] shown in Fig. 2. If the energy and protein level is below 75% of the previously defined requirement for a maximum of 7 days, a re-evaluation takes place and oral nutritional supplements may be used. If there is an indication for additional action such as enteral or parenteral nutrition, this will also be initiated. If enteral feeding via tube is refused by the patient or if the use of a tube is contraindicated from a medical point of view, parenteral nutrition will be started in consultation with the study patient and the physician. In addition to macronutrients, nutritional therapy always ensures an adequate supply of micronutrients. If study patients of both groups (experimental and control) still need nutritional therapy after intervention period, it will be ensured as part of the usual medical care system.

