Exercise training is scheduled 2 times a week (separated by at least 48 h) for a total duration of 60 min. The program targets all major muscle groups, however, emphasis will be put on the lower extremities, as they are primarily affected by the GvHD treatment. The focus of the resistance training will be on muscle hypertrophy. The progressive program for participants who will train at facility centers comprises of 6–8 machine-based exercises, each performed in two sets, 12 repetitions at 60–80% of one repetition maximum (1-RM). For participants who train online, the individual training load will be defined during the introductory training session with the aim of choosing a load which to perform two times 12 repetitions. Patients will be coached in correct techniques for each exercise. Resting time between sets will be 1–2 min, and contractions will be performed at moderate velocities. The exercise intensity will be continuously adapted throughout the 24 weeks. The training is progressive in terms of weight increase to the next machine weight level (at least by 5%) after successfully completing two sets of an exercise with 12 repetitions in three consecutive exercise sessions. If deteriorations occur, the weights will be decreased, if two sets of an exercise within 12 repetitions in two consecutive exercise sessions cannot be attained. Participants will be contacted when 2 session in a row were not joined, without reasoning. Compliance with the exercise program will be determined via self-reported and objective measures such as attendance, exercise logs, target intensity.

Before and after each training session, participants will be asked to complete an exercise log. The physical activity log will be used for exercise monitoring and for adjusting. Moreover, it will be used as a measure of additional physical activity outside of the exercise intervention (such physical activity is not restricted or prohibited). Patients will be asked to report their perceived health status prior and after the training session as well as problem or symptom occurrence related to the exercise program. Further, the performed sets and repetition as well as the perceived exertion of each exercise and discomfort will be recorded. Every 4 weeks patients are instructed to drop off the logs during outpatient visit.

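### Hand grip serves two secondary outcomes, muscle strength and nutritional status, so a training gain in grip could be reported as a nutritional benefit

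*Protocol article*

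**What the plan says.** Table 1 (Study outcomes) lists muscle strength and nutritional status as two secondary endpoints, each assessed from t0 to t4. The instruments for muscle strength are "Hand-grip test, Hand-held Dynamometer". Those for nutritional status are "NRS 2002, hand- grip test, serum albumin, total protein levels".

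The section on nutritional status points back to the strength section for the method: "hand grip strength (see section muscle strength), known as a marker of muscle function and good nutritional state is performed regularly".

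The study design section expects the experimental arm to have better muscle strength and, as a separate item, "a better nutritional status as well as a better submaximal endurance capacity compared to the control group".

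Both arms receive the nutritional programme. According to the abstract, "Subjects of the control group solely receive nutritional support/therapy based on individual needs"; the experimental arm adds supervised resistance training. Of that training the article says "The program targets all major muscle groups", and the same sentence goes on to put the emphasis on the legs.

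The nutritional intervention section says that, during the study, "nutritional recommendations and therapy will be adapted based on the risk of malnutrition". Among the criteria it names "low hand grip strength (men < 30 kg; women < 20 kg"), next to NRS 2002, serum albumin and total protein.

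**The concern.** Where nobody is being trained, hand grip may be a reasonable marker of nutritional state. In this trial strength training is the randomised difference, and grip is one of the strength outcomes chosen to detect its effect. If grip rises more in the experimental arm, the trial cannot tell from grip whether nutrition improved or muscles were trained. Under the present table the same result can be put forward for both hypotheses. The dissemination section plans further publications because of the number of secondary outcomes, so one finding could appear under two headings.

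What is at stake is the answer to the nutritional-status hypothesis. A second, smaller matter is that grip also sits among the criteria for adapting nutritional therapy. A variable that training may move could then influence the nutritional care given, although the trial is meant to compare exercise plus nutrition with nutrition alone.

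**Working it through.** The point contests no stated figure, so there is none to reproduce. The check sets the sections side by side.

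1. *Is it one measurement?* Yes. Table 1 names the hand-grip test in both rows with the same visits, and the nutritional status section refers to the strength section instead of describing a separate test.
2. *Are the two outcomes hypothesised separately?* Yes. The study design section lists strength and nutritional status as distinct expected benefits.
3. *Can the randomised treatment move grip without a change in nutrition?* It can plausibly do so, since all major muscle groups are trained. The leg emphasis makes the size uncertain, and the article gives no expected grip effect.
4. *How much of the nutritional outcome is involved?* One of four listed indicators. No composite score and no improved/not-improved rule is defined. The stated metrics are the difference between arms and the change from baseline to t3. Removing grip leaves 4 − 1 = 3 indicators.
5. *Does grip enter the primary endpoint?* No. The SPPB consists of gait speed, chair stands and balance.
6. *Could the therapy criterion differ by arm?* Only where a patient crosses the 30 kg or 20 kg cut-off and grip is the deciding criterion. The section does not say whether its criteria are joined by *and* or by *or*.

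For step 6, an illustration shows how far a grip gain could shift the number of patients classed as low. The article gives no mean, standard deviation or training effect for grip, so every input except the cut-offs is an assumption. With normally distributed grip, mean μ, standard deviation σ, cut-off c and a pure training gain δ:

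share below cut-off = Φ((c − μ − δ)/σ)

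| Group | c (kg) | Assumed μ (kg) | Assumed σ (kg) | Share below, δ = 0 | Share below, δ = 2 kg | Fewer classed as low |
|---|---|---|---|---|---|---|
| Men | 30 | 28 to 36 | 8 to 10 | 23% to 60% | 16% to 50% | 6 to 10 points |
| Women | 20 | 18 to 26 | 6 | 16% to 63% | 9% to 50% | 7 to 13 points |

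Worked example for men with μ = 32 and σ = 8: Φ((30 − 32)/8) = 40.1% with no gain, and Φ((30 − 34)/8) = 30.9% with a 2 kg gain, a drop of 9.2 points.

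Over the same range for men, a gain of 1 kg gives a drop of about 3 to 5 points and a gain of 4 kg about 12 to 20 points. With no gain in grip the drop is zero. These shares describe who is classed as low on grip. They do not describe who receives different nutrition, which depends on the other criteria.

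**The case against.** The authors can say that grip belongs to the construct they chose. They call it a marker of both muscle function and nutritional state, and their background describes malnutrition as often involving cachexia, with loss of muscle mass and function. That defends grip as a clinical marker. It does not make a between-arm difference attributable to nutrition when strength training is what was randomised.

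They can also say that three other indicators remain, that the programme emphasises the legs, and that the project is described as exploratory. All of this stands and limits the size of the point. It also stands that NRS 2002, albumin and total protein are themselves both outcomes and therapy criteria. Removing grip therefore does not end the overlap between outcome and criterion. It removes the one indicator that is itself a strength outcome of the training.

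Four stronger readings are tempting, and the document supports none of them:

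- *A patient who passes the grip cut-off counts as nutritionally improved.* The cut-off appears only in the therapy section; no such outcome rule exists.
- *Nutrition will differ between the arms.* How the criteria combine is not stated, and several routes to care do not depend on grip: counselling based on NRS 2002, weekly checks of calorie and protein needs, re-evaluation when intake falls below 75% of requirement, and weekly contact. Nutrition is individualised in both arms and was never meant to be identical in amount. If grip did make a difference, controls would tend to keep more support, which would work against the experimental arm.
- *Nutrition delivered cannot be compared because Table 1 lists no record of it.* A condensed article commonly leaves such detail to the full protocol, and the weekly counselling and the 75% rule imply that intake is assessed.
- *The primary comparison is compromised.* The SPPB could be touched only indirectly, if the nutrition given came to differ by arm.

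**Conclusion.** The point holds for the secondary outcome. One hand-grip measurement serves two separately hypothesised outcomes, and the randomised treatment may move it directly, so an arm difference in grip should not be read as evidence of better nutritional status. It affects one of four nutritional indicators. The conclusion rests on the assumption that whole-body resistance training can raise grip. The article makes this plausible by using grip as a strength outcome, but gives it no size.

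The therapy criterion is a secondary note: nutritional care could differ by arm where grip is decisive, and the document does not allow the extent to be estimated. The sample size is not involved.

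**What to change.** In Table 1, list hand grip once, under muscle strength. Base the between-arm comparison of nutritional status on NRS 2002, serum albumin and total protein, and make the hypothesis in the study design section refer to those measures. If grip is still shown beside the nutritional results, label it as the same measurement and do not count it as support for the nutritional hypothesis.

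For the therapy criterion, the sponsor should state how the use of grip fits the comparison of exercise plus nutrition with nutrition alone, and reconcile the sections accordingly. The clinical rule itself is for the sponsor to settle. Nutritional support can be described by arm from the weekly contacts already planned, so that readers can see whether care was similar.

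The cost is a change of wording, one fewer nutritional indicator, and a small effort to summarise information that weekly counselling should already produce. Sample size, visits and the primary analysis stay as they are.
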